#### 4.7.2 Identification of low birth weight

*Low birth weight* is defined as first weight recorded within hours of birth at  $< 2500$  grams. It comprises *very low birth weight* ( $< 1500$  grams) and *extremely low birth weight* ( $< 1000$  grams) [15].

#### 4.7.3 Identification of neonatal death

Neonatal death is defined as death of a live born child within 28 days of birth. It comprises neonatal death in *non-viable live births*, *extremely preterm live births*, *preterm live births* ( $\geq 28$  weeks to  $< 37$  weeks), and in *term live births* [18].

Gestational ages cut-offs will be used regarding what is considered a non-viable live birth at each site/country.

#### 4.7.4 Identification of neonatal infection

Neonatal infection is defined as an *invasive bloodstream infection*, *respiratory infection* or *meningitis* within 28 days of birth [14].

#### 4.7.5 Identification of preterm birth

Preterm birth is defined as gestational age at birth of  $< 37$  weeks [19].

#### 4.7.6 Identification of small for gestational age

Small for gestational age is defined as birth weight below 10th percentile for gestational age [16].

#### 4.7.7 Identification of stillbirth

Stillbirth is defined as foetal death occurring before birth after a selected, predefined duration of gestation. It comprises intrapartum stillbirth and antepartum stillbirth [17].

#### 4.7.8 Ascertainment of vaccine exposure

To assess whether sites are able to determine whether a vaccine had been administered during pregnancy or within 30 days prior to the last menstrual period (LMP). Maternal vaccination status for tetanus or any other vaccines administered during pregnancy will be ascertained for all mothers of identified cases with the health outcome of interest.

A mother who has any mention of maternal vaccination will be considered vaccinated (exposed). This could be a formal recording of vaccination or any other mention in the documents available to the sites.

A mother who has documented evidence of absence of maternal vaccination will be considered non-vaccinated (non-exposed).

Any mother without any indication will be considered to have exposure status 'unknown'.

## 4.8 Data sources

### *Number of live births*

The number of live births at each site, for a period of one year will be ascertained using data from maternity wards.

### *Case identification*

Cases will be identified based on manual review of registries and medical records from maternity and pediatric wards and neonatal intensive care units, through free text search or using ICD9 or ICD10 codes (Annex 4). Registries of interest include, but are not limited to, delivery, admission and discharge registries. Data sources vary between health outcomes and between sites, subject to relevance and availability. All relevant data sources to which a site has access may be used. Data collected during this prospective study must be based on data recorded on the appropriate source documents.

### *CRF completion*

Individual patient records from the mother and the child (including medical records, antenatal care records, antenatal care card, vaccination records), will be used to complete the CRFs.

### *Factors that potentially affect classification*

Information on factors that potentially affect classification were collected through a one-off questionnaire that will be completed once by each site. This will include questions on:

- Health facility level (primary, secondary, tertiary/referral)
- Health facility type (public, private)
- Qualification of staff to identify cases and to complete CRFs
- Availability of technical equipment (e.g. laboratory, ultrasound, type of scale etc.)
- Record keeping.

In addition, the questionnaire will contain a question on the gestational age cut-off that is considered non-viable live birth at each site/country (see section 4.6.3).

## 4.9 Data collection

Each delivery that takes place at the site will be registered and the occurrence of any outcomes of interest within 28 days of birth will be recorded in the electronic data capture system (EDC). In addition, the sex, birth weight, gestational age and the head circumference will be collected. From this, the total number of live births over one year and the total number of cases identified among those delivered at the site will be derived.

Once an outcome occurs and the inclusion and exclusion criteria are met (including informed consent), the infant enters the study. At each site, cases with outcomes of interest will be consecutively recruited into the study, until 100 cases for each outcome have been recruited, or the end of the study period is reached, whichever occurs first.

One infant may present with more than one outcome under study; cases will be recruited for all outcomes until 100 cases for each outcome has been reached. . Data on case ascertainment for each case and maternal vaccination status of the case's mother will be collected in an electronic CRF in an electronic data capture (EDC) system. CRFs are available in Annex 5. If necessary, a paper CRF may be used as an intermediary step.

The EDC system will generate a unique ID for each child. Forms for child and mother shall be automatically linked to this unique ID where appropriate. Country and site codes shall also be assigned by the data management centre.

Investigators at the sites need to be able to link the mother-child pair enrolled in the study with their respective medical records (including vaccination records for the mother). To this end, a password-protected Excel/CSV file containing the mother-child pair's study number and personal data required for unequivocal patient identification (name and surname, gender, date of birth, unique personal identification number if available) will be created and kept locally. No additional data will be included in this file. This file will never leave the site or be shared with anybody not involved in the investigation. This file will be stored in the tablet in which the EDC application will be installed. The EDC will be able to read the file when required during data collection at the site. Access to the files stored in the tablet will be restricted to authorised staff at the site only, and the EDC will not upload the file on the centralized study server. Backup of the file and source documents will be maintained at study sites on periodic basis.

Harmonized data collection procedures will be described in a specific manual of study procedures.

#### 4.10 Case classification

Identified cases and exposures will be classified using the Brighton Collaboration ABC tool (Automatic Brighton Classification) [20] according to the levels of diagnostic certainty present in the GAIA definitions (Level 1-3, and Level 4-5 when applicable).

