## 5.2 Data analysis: Primary study outcomes

### 5.2.1 Primary study outcome 1 – Minimum detectable risk

The minimum detectable risk that can be detected for each health outcome in a future study will be quantified for each GAIA case definition. The minimum detectable risk will be the minimum detectable odds ratio (OR) in a case-control study design and the minimum detectable relative risk (RR) in a cohort study design. This information will be useful to establish the sample size that can be achieved in a one-year period for a specific health outcome in future studies, and the minimum detectable risk that could be achieved. Note that the data collected on maternal vaccination during the study will not be used in this calculation, as this data were collected solely to assess the applicability, and not to assess risk associated with maternal vaccinations currently in use.

For the case-control study design, the minimum detectable OR for each health outcome will be calculated based on:

- Number of cases classified during the study period,
- Different theoretical levels of exposure (maternal vaccination) among cases and controls,
- The ratio of cases to controls,
- 80% power and 95% confidence level,
- Per year of study duration.

For the cohort study design, the minimum detectable RR for each health outcome will be calculated based on:

- Different theoretical percentages of exposed (maternal vaccination) and non-exposed (no maternal vaccination) with each health outcome,
- Different theoretical levels of exposed to unexposed ratio,
- 80% power and 95% confidence level,
- Per year of study duration

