## 5.2.2 Primary study outcome 2: Applicability of GAIA case definition

### 5.2.2.1 Health outcomes

For each health outcome, applicability of GAIA case definition will be assessed by calculating the proportion of cases identified that can be classified according to the GAIA case definition.

The denominator will be the number of cases identified for which the CRF was completed for one health outcome; the numerator will be the number of cases identified for that health outcome that can be classified according to the GAIA case definition.

The applicability of the GAIA case definitions for each health outcome will be reported overall, and stratified by site/country/region, and by health facility level (primary/secondary/tertiary).

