## 5.3 Secondary study outcomes

### 5.3.1 Secondary study outcome 1 – Proportion of cases classified by level

#### 5.3.1.1 Health outcomes

For each health outcome, the proportion of cases that can be classified according to each GAIA case definition level will be assessed.

*Proportion of cases identified that can be classified by level*

- For each health outcome, the proportion of cases identified that can be classified according to each GAIA case definition level will be assessed.

---

 In this document, 'classified' will mean 'classified according to the GAIA case definitions'

- The denominator will be the number of cases *identified* for one outcome; the numerator will be the number of classified cases for each level of the GAIA case definition.

*Proportion of cases classified by level*

- For each health outcome, the proportion of cases classified by level will be calculated.
- The denominator will be the number of cases *classified* for one outcome for all levels; the numerator will be the number of classified cases for each level of the GAIA case definition.

These proportions will be reported overall, and stratified by site/country/region, and by health facility level (primary/secondary/tertiary).

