#### Level 5 of diagnostic certainty

- No evidence of SGA or a confirmed diagnosis other than SGA

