- Gestational age within pre-defined range for selected stillbirth definition as assessed by maternal and/or fetal parameters (Level 1–2 in GA assessment algorithm).

### Level 3

- Delivery of an infant reported to have no of signs of life at birth (No spontaneous movements, no umbilical cord pulse, no heartbeat, no cry or spontaneous respirations, no chest movement, and whole body cyanosis).

AND

- Maternal report of lack of fetal movement for 24 h or more prior to delivery.

OR

- Report of auscultation for fetal heart tones (using electronic or non-electronic devices) documenting lack of fetal heartbeat.

AND

- Non-attended delivery followed by physical examination of the fetus after birth consistent with antepartum death by a health care professional appropriate to the level of standard of care in the health care setting.

OR

- Verbal history by a trained health care provider, non-medical witness or the mother of a fetus born with no signs of life or unresponsive to resuscitation efforts immediately after birth and with physical features consistent with antepartum death.

AND

- Gestational age within pre-defined range for selected stillbirth definition as assessed by maternal and/or fetal parameters (Level 2–3 in GA assessment algorithm).

### Level 4

- Report of stillbirth but fetus is not available for physical examination after birth (no objective assessment can be made).
- Maternal information insufficient to assess gestational age.

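### SGA Level 5, which means the infant is not SGA, counts as 'classified' and so enters the SGA applicability numerator and the case count for the case-control odds ratio

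*Protocol*

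**What the plan says.** Five places in the protocol combine.

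- **Section 4.10** assigns levels to identified cases "according to the levels of diagnostic certainty present in the GAIA definitions (Level 1-3, and Level 4-5 when applicable").
- **Footnote 1 (section 5.3.1.1)** gives the only definition of the key word: "In this document, 'classified' will mean 'classified according to the GAIA case definitions". It sets no limit on levels.
- **Section 5.2.2.1** defines applicability, the second primary outcome. For the denominator: "The denominator will be the number of cases identified for which the CRF was completed for one health outcome". For the numerator: "the numerator will be the number of cases identified for that health outcome that can be classified according to the GAIA case definition".
- **Section 5.3.1.1** also reports the distribution over levels among classified cases, with the denominator taken "for one outcome for all levels".
- **Section 5.2.1** lists among the inputs to the case-control minimum detectable OR: "Number of cases classified during the study period".

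Annex III gives SGA a Level 5: "No evidence of SGA or a confirmed diagnosis other than SGA". No other definition in the annex has one.

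Section 5.4.2 points the other way. It treats Levels 3 and 4 as the lowest levels at which a case is classifiable and does not mention Level 5.

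**The concern.** Levels 1 to 4 grade how well a diagnosis of SGA is supported. Level 5 says that the diagnosis is unsupported or has been replaced by another. If an infant at Level 5 is 'classified', a refuted diagnosis is scored as a success of the SGA definition and then as an SGA case available to a future study. Both primary objectives are touched, and both errors flatter the result: applicability looks higher and the detectable OR looks smaller.

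The cell need not be empty. Section 4.8 allows identification by free text or ICD code. The SGA code list in Annex IV includes unspecified slow fetal growth, and fetal malnutrition with no mention of small or light for gestational age. Some infants found through such entries may prove not to be below the 10th percentile.

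Level 5 infants would also escape the exploratory analyses. Being 'classified', they drop out of the tabulation of unclassifiable cases (section 5.4.1). Not being Level 3 or 4, they fall outside section 5.4.2.

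**Working it through.** **1. The plan's own figure.** Table 1 in section 5.1.2 follows from n = z² p(1−p)/d², with z = 1.96 and d the absolute half-width. For p = 0.50 and d = 0.10, n = 3.8415 × 0.25 / 0.01 = 96.04, rounded up to 97 as stated. The other cells reproduce too, with one rounding difference (384.15 shown as 384). No stated number is wrong; the problem is what gets counted.

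**2. Does any text remove Level 5?** Section 4.10 puts it in the set of levels, footnote 1 does not take it out, and sections 5.2.2.1, 5.3.1.1 and 5.2.1 use 'classified' without restriction. Section 5.4.2 conflicts with this but states no exclusion.

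**3. Applicability.** Let N be identified SGA cases with a completed CRF, A the number at Levels 1-4, and F the number at Level 5.

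- As written: (A + F)/N
- Level 5 not counted: A/N
- Difference: F/N, one percentage point per 1% of cases at Level 5

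The documents give neither A nor F. With N = 100 and A = 50 assumed:

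| Level 5 share (assumed) | As written | Level 5 not counted |
|---|---|---|
| 5% | 55% | 50% |
| 10% | 60% | 50% |
| 20% | 70% | 50% |
| 30% | 80% | 50% |

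**4. Minimum detectable OR, case-control.** Section 5.2.1 sets 80% power and 95% confidence (taken as two-sided 5%). Exposure among controls p0 and 1:1 matching of numbers are assumptions. For n cases and n controls:

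- p1 = OR·p0 / (1 − p0 + OR·p0), and p̄ = (p1 + p0)/2
- power = Φ{ [p1 − p0 − 1.96·√(2p̄(1−p̄)/n)] / √([p1(1−p1) + p0(1−p0)]/n) }

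The OR is solved for power 0.80. At p0 = 0.50:

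- n = 100, OR 2.26: p1 = 1.13/1.63 = 0.693; (0.193 − 1.96 × 0.0694)/0.0680 = 0.84; power 0.80.
- n = 80, OR 2.51: p1 = 2.51/3.51 = 0.715; (0.215 − 1.96 × 0.0772)/0.0753 = 0.85; power 0.80.

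If 100 'classified' cases include Level 5 infants:

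| Exposure in controls | Reported (100) | 10 at Level 5 (90) | 20 at Level 5 (80) | 30 at Level 5 (70) |
|---|---|---|---|---|
| 20% | 2.44 | 2.55 | 2.69 | 2.86 |
| 50% | 2.26 | 2.37 | 2.51 | 2.68 |
| 80% | 3.53 | 3.89 | 4.41 | 5.21 |

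With 80 true cases, power at the reported OR of 2.26 is 71%, not 80%. Pooled over 25 sites at the cap of 100 each (2,500 classified, 2,000 true), the OR at 50% exposure moves only from 1.17 to 1.19. The distortion matters mainly at site level.

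**5. Cohort relative risk.** The inputs listed in section 5.2.1 for this design contain no count of classified cases, so no effect is shown there.

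**The case against.** The best defence is that the protocol's usage elsewhere implies Level 5 is not meant to count. Section 5.4.1 treats being unclassifiable as not meeting the definition, section 3.3 speaks of cases failing to reach the definition's lowest level of certainty, and section 5.4.2 stops at Level 4. The analyst may well exclude Level 5. This stands as evidence of intent, but it contradicts section 4.10 and does not amend it. The matter is also not one left open for the analysis plan, because the protocol itself fixes the level range, the meaning of 'classified' and the numerator.

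It can also be said that section 5.3.1.1 reports identified cases by level, so a reader could subtract Level 5. That is true, and it limits the harm, but the headline applicability and the OR would still be wrong.

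Three stronger readings are tempting, and the documents do not support them.

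- **That SGA applicability is driven to about 100%.** An infant with recorded weight and gestational age below the 10th percentile, but weighed after 48 hours or on a scale of unknown calibration, misses Levels 1-3. Such an infant does not clearly fit Level 4, and does not fit Level 5 because there is evidence of SGA. Section 5.4.1 expects such a residual.
- **That Level 4 should go as well**, because for SGA and stillbirth it records thin evidence (for stillbirth, for example, "Maternal information insufficient to assess gestational age"). Level 4 is a genuine level of certainty in those definitions, and also in low birth weight and microcephaly. Keeping only Levels 1-3 is a preference.
- **That definitions cannot be compared at all.** The analysis is planned outcome by outcome, and the differing number of levels belongs to the definitions themselves.

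It is also fair that Level 4 already takes chart or code diagnoses without documented weight or gestational age, and that the SGA form in Annex V has no item for an alternative diagnosis. Both may keep Level 5 small.

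**Conclusion.** The point holds for SGA Level 5. Read literally, the protocol counts infants without SGA in the applicability numerator, in the by-level denominator and in the case count for the case-control OR, and this is inconsistent with section 5.4.2. Applicability is overstated by exactly the Level 5 share. At 20 Level 5 infants per 100 classified, the minimum detectable OR is understated as 2.26 against 2.51. The Level 5 share, the exposure and the control ratio are all assumptions, and the text supplies none of them. The other six health outcomes, maternal immunisation and the cohort relative risk are not affected. The correction is narrow, but it concerns both primary outcomes and should be made before analysis.

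**What to change.** - In section 4.10 and footnote 1, define 'classified' as meeting the GAIA definition at Levels 1-4, where the definition has those levels.
- Exclude Level 5 from the applicability numerator (5.2.2.1), the by-level 'classified' denominator (5.3.1.1) and the case-control case count (5.2.1).
- Keep Level 5 infants in the applicability denominator, which section 5.2.2.1 already sets as identified cases with a completed CRF. The choice needs stating because it matters: with 50 of 100 at Levels 1-4 and 20 at Level 5, keeping them gives 50/100 = 50%, and dropping them gives 50/80 = 62.5%.
- Report Level 5 on a separate line as identified but not confirmed.
- Check that sections 4.10, 5.2.1, 5.2.2.1, 5.3.1.1 and 5.4.2 then agree. A Levels 1-3 figure may be added as a supplement, not as a replacement.

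The cost is a few sentences and no new data. To the extent that Level 5 is used, the SGA applicability figure and the minimum detectable OR become slightly less favourable.

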## 5 Statistical methods

Data will be analysed by objective and by health outcome, using appropriate statistical software (e.g. SAS, R, SPSS).

### 5.1 Sample size

#### 5.1.1 Primary study outcome 1: Minimum detectable risk

No sample size calculation is required for this outcome. All cases identified during the study period will be included in the study.

#### 5.1.2 Primary study outcome 2: Applicability of GAIA case definitions

Sample size estimations for these outcomes are provided as an indication of the precision level that can be achieved, depending on the number of cases identified per health outcome per site during the study period.

Table 1 shows the number of cases required for different levels of precision and expected proportions of applicability.

*Table 1. Number of cases required for different levels of precision*

| Relative precision | Expected proportions (applicability) |     |     |
|--------------------|--------------------------------------|-----|-----|
|                    | 20%                                  | 50% | 80% |
| 10% (+/- 5%)       | 246                                  | 384 | 246 |
| 20% (+/- 10%)      | 62                                   | 97  | 62  |
| 30% (+/- 15%)      | 28                                   | 43  | 28  |
| 40% (+/- 20%)      | 16                                   | 25  | 16  |

Assuming proportions of 50% ('worst case'), 97 cases would enable the calculation of proportions with 20% relative precision.

In the analysis, proportions for the primary analysis will be calculated overall and stratified by site, country, region, health facility level of care. The smallest unit is the site. Therefore, 97 cases per outcome per site would be required for 20% precision around proportions of 50%.

For this reason, we aim to enroll 100 cases per outcome per site. Failure to achieve the target of 100 for some outcomes and sites due to a low occurrence of the outcome under study will result in a loss of precision.

For some sites and outcomes, the number of subjects identified with the outcome of interest may exceed 100 during the study period. At each site, cases with outcomes of interest will be consecutively recruited into the study, until 100 cases for each outcome have been recruited, or the end of the study period is reached, whichever occurs first.

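### Table 1 calls its precision relative, but every cell is computed for an absolute half-width; the sizes can stand once the scale is renamed

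*Protocol*

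**What the plan says.** Protocol section 5.1.2 offers Table 1 to show what precision can be reached for the applicability proportions (primary outcome 2), given the number of cases found per outcome and site. The rows are headed "Relative precision" and read 10% (±5%), 20% (±10%), 30% (±15%) and 40% (±20%). The columns are expected applicability of 20%, 50% and 80%. The same ± value serves all three columns.

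Below the table, the text takes 50% as the worst case and says that "97 cases would enable the calculation of proportions with 20% relative precision". Because the site is the smallest unit of analysis, it continues: "Therefore, 97 cases per outcome per site would be required for 20% precision around proportions of 50"%. From this it concludes that "we aim to enroll 100 cases per outcome per site", and warns that sites short of the target will lose precision.

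**The concern.** Relative precision expresses the half-width as a fraction of the proportion itself. For a fixed relative precision, the required number of cases must rise as the proportion falls. Table 1 instead gives identical numbers at 20% and 80%, for example 62 in both columns of the second row. That symmetry belongs to absolute precision, where the variance p(1−p) peaks at 50%.

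Stating precision is the table's whole purpose. The smaller rows matter because some sites are expected to fall short of 100 cases for rarer outcomes. Low applicability is also a real possibility: section 2.1 notes that some definitions may ask for more than a site can provide clinically. A site with 28 cases and 20% applicability would find itself in a row labelled 30% relative precision, when the true relative figure is about 74%.

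**Working it through.** **Inputs.** From section 5.1.2: the row labels and their ± values, the expected proportions of 20%, 50% and 80%, the twelve printed sizes and the target of 100. The section gives no confidence level. I assume two-sided 95% (z = 1.96, unrounded in the computation). The protocol's only explicit statement, "80% power and 95% confidence level", is in section 5.2.1 and concerns primary outcome 1, but the same level reproduces this table.

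**Step 1: reproduce the table on the absolute scale.** Formula: n = z² p(1−p)/d², with d the half-width.

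| d | p = 20% | p = 50% | p = 80% | Printed |
|---|---|---|---|---|
| 0.05 | 245.85 | 384.15 | 245.85 | 246 / 384 / 246 |
| 0.10 | 61.46 | 96.04 | 61.46 | 62 / 97 / 62 |
| 0.15 | 27.32 | 42.68 | 27.32 | 28 / 43 / 28 |
| 0.20 | 15.37 | 24.01 | 15.37 | 16 / 25 / 16 |

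All twelve cells reproduce. Eleven are rounded up (96.04 to 97, 24.01 to 25). The exception is 384.15, printed as 384; rounding up gives 385.

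**Step 2: try the relative scale.** Here d = r·p, so n = z²(1−p)/(p r²).

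| r | p = 20% | p = 50% | p = 80% |
|---|---|---|---|
| 10% | 1,537 | 385 | 97 |
| 20% | 385 | 97 | 25 |
| 30% | 171 | 43 | 11 |
| 40% | 97 | 25 | 7 |

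Only the 50% column agrees with the printed sizes (apart from the 384/385 rounding), because r × 50% equals the printed ± value there: 20% of 50% is 10 points. At r = 20% and p = 10%, n would be 865. So on the relative scale the requirement keeps growing as p falls, and 50% is not the worst case.

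**Step 3: relative precision that the printed sizes give.** Formula: z√(p(1−p)/n)/p. For example, at p = 20% and n = 62: 1.96 × √(0.16/62) = 0.0996, and 0.0996/0.20 = 49.8%.

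| Label | p = 20% | p = 50% | p = 80% |
|---|---|---|---|
| 10% | 25.0% | 10.0% | 6.2% |
| 20% | 49.8% | 19.9% | 12.4% |
| 30% | 74.1% | 29.9% | 18.5% |
| 40% | 98.0% | 39.2% | 24.5% |

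**Step 4: what the target delivers.** With 97 cases the half-width is 9.95 points at 50%, its maximum over all p. With 100 cases it is 9.8 points at 50% (19.6% relative) and 7.8 points at 20% or 80% (39.2% and 9.8% relative).

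**The case against.** The best defence is that the table shows the scale it used. Each row prints its ± value, and on that scale the sizes and the worst-case remark are right. The first figure in each row is twice the second, so the pair can be read as full interval width and half-width. The sentence with 97 is conditioned on 50%, where 20% relative and ±10 points coincide, so its number is true. No planned analysis uses the 62 in the 20% column.

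Most of this stands, and it makes the defect one of labelling rather than calculation. It does not rescue the label. A full width of 20 points is still an absolute measure, and the word relative appears in both the header and the text.

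A reader might go further and infer three things that the documents do not support:

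- **That 385 cases per site are needed, or that 100 is too few.** This holds only if relative precision was truly intended. Apart from the label, everything points the other way: one ± value across columns, equal sizes at 20% and 80%, and 50% as worst case.
- **That the 80% column also falls short.** It exceeds its label: 62 cases give about 12.4% relative precision, and 25 would suffice for 20%.
- **That the study expects low applicability.** Section 2.1 says only that some definitions may be hard to apply; 20% is one of three illustrative values.

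**Conclusion.** The concern holds as a misnamed scale in the sample-size justification. Read literally, the label is correct at 50% applicability, too favourable at 20% by a factor of about 2.5 in every row (for instance 49.8% against 20%), and too pessimistic at 80%. The worst-case remark is valid only for absolute precision. The 384 is a one-case rounding inconsistency with no consequence.

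The conclusion rests on 95% confidence and the normal approximation, neither stated in section 5.1.2 but together reproducing the whole table. Reading the intended scale as absolute is an inference from the cells, though a strong one. On that reading 97 cases are enough for ±10 points at any proportion, and the target of 100 is sound.

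**What to change.** In section 5.1.2:

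1. Rename the rows of Table 1 as absolute precision: 95% confidence interval half-width of ±5, ±10, ±15 and ±20 percentage points. Drop the leading 10%, 20%, 30% and 40%. This also supplies the missing confidence level.
2. Delete the word relative from the sentence on 97 cases, and change the 20% precision in the per-site sentence to ±10 percentage points. Suggested wording: with 97 cases, the 95% confidence interval half-width is at most 10 percentage points whatever the proportion, the widest case being 50%.
3. Add what the target gives: with 100 cases, 9.8 points at 50%, and 7.8 points at 20% or 80% (about 39% and 10% in relative terms).
4. Print 385 in place of 384 (minor).

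The cost is one column of row labels, one cell and two or three sentences. Recruitment, the 100-case target and the analyses are untouched. The only thing given up is a relative figure that looked more favourable for low applicability than the sizes support.
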